## Abstract

**Background::**

Family caregivers of persons with dementia face significant challenges in navigating hospital-to-community transitions. Community health worker-led interventions offer a promising approach to delivering culturally responsive psychosocial support and care navigation. However, there is limited evidence on the feasibility of implementing care transition interventions for this population across healthcare settings. This single-site, single-arm pilot study evaluates the feasibility, acceptability, and preliminary impact of a community health worker-led care transition intervention for caregivers of persons with dementia, Connecting and Empowering Persons living with Dementia and cARegivers during Transition (CEDART).

**Methods::**

Forty hospitalized persons with dementia and their caregivers will receive the CEDART intervention. Eligible patients with confirmed or suspected dementia will be enrolled from a Texas hospital. Respective caregivers will then participate in an initial assessment meeting followed by individualized care planning and follow-up meetings led by the community health worker. The community health worker will continue to provide caregivers with tailored dementia care education, emotional support, and connections to community resources for up to three months post-discharge. Input from a community advisory board of hospital system partners, community-based service providers, and dementia care experts - alongside key informant interviews with hospital providers, community providers, and caregiver participants receiving CEDART intervention, will be used to evaluate the acceptability of the intervention. Key informant interviews will be conducted to assess whether the intervention meets and addresses stakeholder priorities. Participating caregivers will complete baseline, 6-week, and 12-week follow-up interviews to assess caregiver outcomes and intervention feasibility and acceptability.

**Conclusions::**

Study findings will be used to evaluate the feasibility and acceptability of the proposed CEDART care transition intervention for persons with dementia and family caregivers. These results will inform the design of a future definitive randomized control trial.

**Trial registration:**

NCT06831318 (registered and posted on ClinicalTrials.gov)

## Background

Transitions of care refer to the process of moving patients between health care practitioners, various care settings, and home as their care needs change [1]. Hospital-based care transitions (i.e., leaving the hospital for care elsewhere) pose significant risks for patients’ safety [2]. Most notably, persons with dementia are 1.5 – 2 times more likely than non-dementia peers to be hospitalized [3, 4]. This heightened risk can make the care transition process especially fraught and challenging. For persons with dementia, such transitions often involve short-term stays in skilled nursing facilities before returning home [5]. With each transfer from one care setting to another, the risk of medical errors, incongruent or unnecessary medical treatments, and hospital readmission increases [6–8]. During these transitions, family caregivers play crucial roles in the care of persons with dementia [9, 10]. Thus, it is critical to engage and collaborate with family caregivers to ensure safe care transitions across healthcare settings.

Transitional care interventions include the delivery of time-limited services to promote continuity and coordination of healthcare. These interventions have been shown to improve patient outcomes across diverse health conditions, including heart failure, chronic obstructive pulmonary disease, acute myocardial infarction, and stroke [11–17]. However, persons with dementia have been underrepresented in this body of research. Although many assume that the question of how to improve care transition outcomes has been answered, transitional care interventions are underutilized or insufficiently adapted for persons with dementia and their family caregivers [9, 18]. Current transitional care models for persons with dementia are limited in number and tend to be broadly designed, often involving complex, multiple TC support types (i.e., patient education, medication reconciliation, referral to community-resources, home visits) delivered over extended periods (e.g., months to years). Some hospital-based transitional care models have shown efficacy for persons with dementia[19], but their complexity and resource demands limit scalability and wider adoption.

To address these challenges, we developed our hospital-based care transition intervention, **C**onnecting and **E**mpowering Persons living with **D**ementia and c**AR**egivers during **T**ransition (CEDART), to be delivered by a community health worker for use in a future definitive randomized control trial. Community health workers [20–22] are lay community members who work—either paid or voluntarily—with local health systems in urban and rural settings. Community health workers are viewed as trusted allies of their respective communities through shared ethnicity, language, socioeconomic background, and/or experiences with those they serve. Thus, they can effectively bridge cultural gaps between vulnerable patients, family caregivers, and the healthcare system to holistically address caregiving needs [23–28]. Community health workers also have the capacity to provide pragmatic caregiving advice, information, and individualized support for family caregivers, thereby fostering their self-efficacy and resilience. Given their role as resource connectors and trusted community members, community health workers are equipped to deliver culturally responsive, effective care transition interventions. Our community health worker-led approach is further informed by the Sociocultural Stress and Coping Model [29], Roberts’ Crisis Intervention Model [30], and evidence from the literature on effective components of existing care transition models [16].

## Methods

### Study aim

This study will evaluate feasibility and inform the optimal design of a future definitive randomized trial to test the efficacy of the CEDART intervention for persons with dementia and their caregivers during care transitions.

### Objectives

To assess the feasibility and acceptability of the proposed CEDART intervention to participants.To test the feasibility and acceptability of a future definitive trial.

The main hypotheses of the study are:

The community health worker interventionist will adhere to the intervention protocol with a score of 70% or higher on the intervention fidelity checklist throughout the delivery period.Caregiver ratings of our intervention will show that the community health worker interventionist was helpful and satisfactory at the end of the intervention period.The intervention will be feasible, as evidenced by intervention completion rates greater than or equal to 70%. Completion will be defined by the proportion of participants who complete follow-up sessions and complete assessments at baseline, 6-week, and 12-week time points.Patient and caregiver outcomes will show improvement over time, as indicated by positive trends in follow-up data at 6 and 12 weeks compared to baseline.

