### Sample size

As this is a single-arm pilot study, a power analysis was not required. It is suggested that sample sizes for pilot studies be determined based on practical factors such as participant availability, budget constraints, and the number of participants required to sufficiently assess feasibility outcomes [47]. Based on these considerations, a target sample size of 40 caregiver-patient dyads was selected. This sample size accounts for the estimated number of weekly admissions of patients with dementia at the recruiting hospital and the anticipated recruitment timeline.

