### Data analysis

#### Quantitative analysis

All quantitative data analyses (e.g., descriptive statistics, correlations, and linear mixed-effects models) will be conducted using SPSS v24 and RStudio software. To assess the intervention’s potential impact on dyad outcomes, we will perform within-group, longitudinal analyses following an intention-to-treat approach. Changes in outcomes from baseline to 6-week and 12-week follow-up will be examined using linear mixed-effects models to account for repeated measures. A change of 0.3 standard deviation units or greater in key outcome measures will be considered indicative of potential efficacy, consistent with effect sizes observed in similar palliative care pilot studies. Because the nature of the study is exploratory, analysis will focus on in-sample effect size estimation rather than formal hypothesis testing. Statistical power is not a primary concern as no inferential statements will be made, which is consistent with appropriate analytical approaches for pilot study data. To analyze the acceptability and feasibility of the protocol, as well as barriers to recruitment and retention, we will use analytic techniques for mixed methods study such as content analyses and descriptive methods.

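### Main hypothesis 4 rests on positive trends of no stated size, while the analysis section uses a 0.3 SD benchmark and disclaims hypothesis testing; the two are not reconciled

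*Protocol article*

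**What the plan says.** The Objectives section opens its list with "The main hypotheses of the study are". The fourth entry reads "Patient and caregiver outcomes will show improvement over time, as indicated by positive trends in follow-up data at 6 and 12 weeks", relative to baseline. It gives no minimum size, names no measures, and does not say how results on several measures are to be combined.

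The Quantitative analysis section plans mixed models for repeated measures: "Changes in outcomes from baseline to 6-week and 12-week follow-up will be examined using linear mixed-effects models to account for repeated measures". It then sets a benchmark: "A change of 0.3 standard deviation units or greater in key outcome measures will be considered indicative of potential efficacy". It does not say whether the SD is that of baseline scores or of change, which visit counts, or that the change must be in the favourable direction. The same section states that "analysis will focus on in-sample effect size estimation rather than formal hypothesis testing" and that "Statistical power is not a primary concern as no inferential statements will be made".

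The Feasibility study outcomes section places preliminary efficacy among the secondary outcomes. The progression criteria in Table 5 contain neither the trend wording nor the 0.3 SD benchmark.

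**The concern.** The article gives two yardsticks for one question, whether outcomes improved. The hypothesis speaks of direction; the analysis section speaks of direction and size. No sentence says that the second defines the first. The article also calls improvement a main hypothesis while saying that hypotheses will not be formally tested.

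What is at stake is the wording of the final report. A small favourable change could be written up as support for a main hypothesis when, by the plan's own benchmark, it does not indicate potential efficacy. Direction alone is weak evidence, because chance produces a favourable direction often. With no control group, a reader has little else against which to judge such a statement.

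**Working it through.** The article states no alpha, power or error rate for hypothesis 4, and sets the sample size on practical grounds, so there is no figure of its own to reproduce. The check asks how often the two yardsticks part on the same data.

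**Inputs from the article:** 40 dyads (Sample size: "a target sample size of 40 caregiver-patient dyads was selected"); visits at 6 and 12 weeks; benchmark 0.3 SD; attrition below 30% (Table 5), which at its limit leaves 40 × 0.7 = 28 completers.

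**Assumptions not in the article:** equal variances at all visits; correlation r between baseline and follow-up of 0.5 (range 0.3 to 0.7); normally distributed mean change, which suits scale scores better than admission counts.

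**One measure, one visit.** In baseline SD units, SE = sqrt(2(1 − r)/n). With n = 40 and r = 0.5, SE = sqrt(1/40) = 0.158. If the SD of change is meant instead, SE = 1/sqrt(40), the same value. For a true change d:

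- P(favourable) = Φ(d/SE), which is 0.50 when d = 0, whatever n and r are.
- P(change ≥ 0.3 SD) = 1 − Φ((0.3 − d)/SE). At d = 0 and r = 0.5 this is 1 − Φ(1.90) = 0.029.
- P(favourable but below 0.3 SD) is the difference: 0.500 − 0.029 = 0.471.

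| r (n = 40) | SE | P(≥ 0.3 SD), d = 0 | Disagreement, d = 0 | Disagreement, d = 0.15 |
|---|---|---|---|---|
| 0.3 | 0.187 | 0.054 | 0.446 | 0.577 |
| 0.5 | 0.158 | 0.029 | 0.471 | 0.657 |
| 0.7 | 0.122 | 0.007 | 0.493 | 0.779 |

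With 28 completers, d = 0 and r = 0.5, the chance of reaching 0.3 SD is 0.056 and the disagreement is 0.444.

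**One measure, both visits favourable.** With no true change, P = 1/4 + arcsin(ρ)/(2π), where ρ is the correlation between the two change scores. If all three visits correlate equally, ρ = (1 − r)/(2(1 − r)) = 0.5, and P = 1/4 + 1/12 = 0.333. At ρ = 0 it is 0.25 and at ρ = 0.9 it is 0.43. Simulation with 1,000,000 draws at ρ = 0.5 gives these disagreement rates under no change, over r = 0.3 to 0.7:

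- 40 dyads: 0.292 to 0.327 if the benchmark is applied at 12 weeks, and 0.319 to 0.333 if it is applied at both visits.
- 28 completers: 0.271 to 0.316 and 0.305 to 0.329.

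Together this is about 27% to 33%.

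**Several measures.** No combining rule is stated. Take six independent measures, each favourable at both visits with probability 1/3. At least one is favourable with probability 1 − (2/3)^6 = 0.91, and all six with probability (1/3)^6 = 0.001. The answer depends almost wholly on a rule that the article does not give.

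**The benchmark itself.** If the true change is exactly 0.3 SD, the observed change reaches 0.3 SD half the time. It can describe a result but does not work well as a pass mark.

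**The case against.** The strongest reply is that no contradiction exists. Objectives are usually broad and analysis sections make them operational, so 0.3 SD may simply be what a positive trend means here. Alternatively, improvement over time and potential efficacy may be different ideas, and a gain of 0.15 SD could meet one without the other. The article does not say that any trend confirms the hypothesis, nor that hypothesis 4 requires 0.3 SD. It also disclaims inferential statements, so false-positive rates describe a test that it does not plan.

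Much of this stands. The two statements are unreconciled rather than flatly opposed, and the probabilities show how far they can diverge; they are not error rates of a planned test. But neither harmonising reading is written down: the benchmark sentence mentions neither hypothesis 4 nor trends. This is also not a detail left to a fuller document, since both yardsticks appear in the article and differ.

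Three stronger inferences are tempting and unsupported:

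- That hypothesis 4 would be confirmed half the time by chance. This is the one-visit or single-slope reading. The wording names both 6 and 12 weeks, and requiring both gives about one third.
- That it would be confirmed nearly always on some measure. This needs an unstated one-of-six rule and independent measures. With measures correlated 0.5 the figure is 0.72.
- That the decision to proceed to the definitive trial is compromised. Table 5 uses neither yardstick, and its sample-size criterion draws on baseline scores and variability, not on observed change.

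**Conclusion.** The point holds as an unreconciled criterion. For one measure with no true change, 40 dyads and r = 0.5, a favourable direction is 17 times as likely as reaching the benchmark at one visit (0.50 against 0.029), and about 11 times as likely when both visits must be favourable (0.333 against 0.029). The gap is wider for a small real change: at a true 0.15 SD the one-visit criteria disagree about 66% of the time (58% to 78%). These figures rest on the assumed correlation, equal variances and normality. No overall false-confirmation rate can be fixed while the combining rule is unstated.

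The harm is confined to the preliminary-efficacy conclusion, which is secondary and exploratory. It is worth correcting because it changes what the study may claim, and the correction is nearly free.

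**What to change.** In the Objectives, delete the clause that makes positive trends the indicator of improvement, and recast hypothesis 4 as an estimation objective. Suggested wording: the mean change from baseline to 6 weeks and to 12 weeks will be estimated in baseline SD units with a 95% confidence interval; no hypothesis of improvement is tested. Keep 0.3 SD, in the favourable direction of each scale, as the single descriptive benchmark, and state it identically in the Objectives and the Quantitative analysis section. Add there that the intervals show precision and are not used as tests, so that they sit with the statement on inference.

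The cost is wording only: no change to data collection, visits or sample size. The downside is that hypothesis 4 can no longer be reported as confirmed on direction alone.

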### Design

This study will use a nonrandomized feasibility design and will follow the SPIRIT 2013 [31] guidelines and reporting template [see Additional file 1]. Enrollment, intervention, and assessment timelines are displayed in Table 1. The CONSORT extension guidelines and checklists were also adapted for the purpose of the study protocol [see Additional File 2]. The CONSORT flow diagram in Figure 1 depicts the participant flow in our intervention.

Specifically, the study is designed as a single-site, single-arm feasibility study with 40 hospitalized patient-caregiver dyads receiving the CEDART intervention over a three-month period. All hospitalized dyads will be recruited from a medical school-affiliated hospital located in Austin, Texas, which is part of a large U.S. healthcare system. We will obtain preliminary data on the intervention’s acceptability, feasibility, and potential efficacy at the end of the study period. Additional insights will be gathered through interviews with key informants, who will be recruited from the hospital that is a main recruitment site, another hospital within the same healthcare system, and the surrounding community. Inclusion and exclusion criteria for eligible family caregivers and persons with dementia can be found in Table 2.

### Participants

#### Hospitalized persons with dementia

Inclusion criteria

Aged 50 or olderHas confirmed or suspected dementia or cognitive impairmentScores 4–6 on Functional Assessment Staging Tool [32]Admitted to the hospital from homeEnglish- or Spanish-speaking

#### Family Caregivers

Inclusion criteria

Aged 18 or olderEnglish- or Spanish-speakingIdentifies as the patient’s relative or partner who assists with medical care on a regular, unpaid basis

#### Key Informants: (Hospital Staff)

Inclusion criteria

Aged 18 or olderEnglish-speakingAffiliated or employed full-time or part-time at two hospitals in Austin, TexasInvolved directly or indirectly with patient care (i.e., nurses, physicians, physician assistants, care managers, social workers, chaplains, discharge planners, information technology staff, administrative managers).

#### Key Informants: Family Caregivers

Inclusion criteria

Aged 18 or olderEnglish- or Spanish-speakingCurrently or previously cared for a relative with dementia

#### Key Informants: Content Expects or Community Service Providers

Inclusion criteria

Aged 18 or olderEnglish- or Spanish-speakingIdentified as having expertise in dementia care or related areas (e.g., aging service providers, staff at Alzheimer’s Association, scholars in aging, dementia, caregiving, or care transition)

### Conceptual Model

Our CEDART intervention model was designed with an understanding of the dynamic, longitudinal, and often complex nature of care transitions. While the standardization of transitional care interventions may be useful in terms of replicability and scalability, effective interventions must be adaptable and individualized to each patient-caregiver dyad. Successful care transition interventions also anticipate and address emergent care needs, rather than strictly adhering to a predetermined care plan. Thus, our current model integrates key concepts from the Sociocultural Stress and Coping Model and Roberts’ Crisis Intervention Model to maximize effective intervention delivery and adaptability. The Sociocultural Stress and Coping Model [20] provides a comprehensive lens to examine the role of sociocultural influences and social determinants of health on persons with dementia and caregiver outcomes. Research on dementia caregiving, including our own work, suggests that factors such as caregiving network size, distrust of healthcare systems, and social determinants of health shape how persons with dementia and caregivers adjust to care transition processes and implement healthcare provider recommendations [33–38]. These factors can therefore significantly impact patient and caregiver outcomes. Accordingly, the community health worker interventionist must systematically assess contextual characteristics of patient-caregiver dyads to identify their unique support needs, potential barriers to accessing informal and formal services, and strategies to address any unmet needs.

Roberts’ Crisis Intervention Model [30] informs the overall process and steps of establishing rapport, as well as conducting assessments, care planning, and follow-ups with the family caregiver. Therefore, an effective intervention approach requires addressing each step in this framework, though caregivers may not follow these steps sequentially. For instance, a caregiver may revisit earlier stages of the model, such as exploring feelings, during later stages like planning. This flexibility is normal and does not reflect ineffective support. Given that continuous assessment throughout the intervention is critical, the community health worker is expected to regularly confirm whether caregivers’ evolving needs, priorities, and emotions are being addressed.

### Conceptual Model

Our CEDART intervention model was designed with an understanding of the dynamic, longitudinal, and often complex nature of care transitions. While the standardization of transitional care interventions may be useful in terms of replicability and scalability, effective interventions must be adaptable and individualized to each patient-caregiver dyad. Successful care transition interventions also anticipate and address emergent care needs, rather than strictly adhering to a predetermined care plan. Thus, our current model integrates key concepts from the Sociocultural Stress and Coping Model and Roberts’ Crisis Intervention Model to maximize effective intervention delivery and adaptability. The Sociocultural Stress and Coping Model [20] provides a comprehensive lens to examine the role of sociocultural influences and social determinants of health on persons with dementia and caregiver outcomes. Research on dementia caregiving, including our own work, suggests that factors such as caregiving network size, distrust of healthcare systems, and social determinants of health shape how persons with dementia and caregivers adjust to care transition processes and implement healthcare provider recommendations [33–38]. These factors can therefore significantly impact patient and caregiver outcomes. Accordingly, the community health worker interventionist must systematically assess contextual characteristics of patient-caregiver dyads to identify their unique support needs, potential barriers to accessing informal and formal services, and strategies to address any unmet needs.

Roberts’ Crisis Intervention Model [30] informs the overall process and steps of establishing rapport, as well as conducting assessments, care planning, and follow-ups with the family caregiver. Therefore, an effective intervention approach requires addressing each step in this framework, though caregivers may not follow these steps sequentially. For instance, a caregiver may revisit earlier stages of the model, such as exploring feelings, during later stages like planning. This flexibility is normal and does not reflect ineffective support. Given that continuous assessment throughout the intervention is critical, the community health worker is expected to regularly confirm whether caregivers’ evolving needs, priorities, and emotions are being addressed.

